### Formative and process data

Study procedures were informed by formative qualitative research conducted with pregnant women attending antenatal care at CHBH prior to the trial inception. We have written standard operating procedures (SOPs) to support the research team to deliver the study procedures and intervention according to the protocol. Participant adherence will be assessed by counts (e.g., visit attendance) and intervention delivery will be monitored by observing contacts between the sonographer (who will conduct the US and deliver the ECD messages) and participants (intervention and control) to record the nature of interactions. We will monitor intervention dose and experience by recording the duration of the ultrasound visit (with and without delivery of the intervention) and by gathering participant and partner views on the ultrasound experience. Ongoing consultation with a key stakeholder network will inform intervention procedures and assist with contextualising the intervention and addressing any challenges that may arise during trial implementation.

Due to the well-documented challenges with engaging men in research and health care in South Africa [54], we will adopt pro-active recruitment strategies, which will include telephone calls to partners after participant enrolment and follow-up calls closer to the visit to encourage attendance. We have also included Saturday sessions for those partners who are unable to attend during the week due to work commitments. Research staff will make regular contact with participants in-between study visits to maintain the accuracy of records and to promote retention of participants in the study. We will follow-up participants who default and those who withdraw to gain an understanding of why they dropped out during the course of the trial.

### Data analysis

All available data at baseline will be analysed descriptively for each intervention group and in total. Categorical data will be summarised by numbers and percentages. Continuous data will be summarised by the mean, SD and range if data are normal and by the median, IQR and range if data are skewed. Minimum and maximum values will also be presented for continuous data. Differences regarding baseline variables will be checked for clinical relevance between the three treatment groups.

A CONSORT flow diagram will be used to summarise the number of participants who were: assessed for eligibility at screening, eligible at screening, eligible and randomised, lost to or discontinued the intervention and included in the primary outcome analysis. If possible, respondents and non-respondents will be compared.

The analysis of the primary outcome will be performed on the intention-to-treat population with no imputation of missing data. In the primary analysis, child development scores will be compared to the control group. If outcome data are normally distributed, we will fit linear regression models. If not normally distributed, outcome data will be categorised and logistic regression methods will be used to assess differences between intervention and control groups. Tests will be two-sided with a significance level of 0.05, and 95% confidence Intervals will also be reported. In case of relevant differences in baseline characteristics, additional adjustment(s) for these factors will be performed within the models to address potential confounding.

A stratified analysis will be done for three pair-wise comparisons—that is, Arm 1 vs. control, Arm 2 vs. control and Arm 1 vs. Arm 2 —according to the following subgroups: partner vs. no partner accompaniment and parity.

STATA, Version 15 (StataCorp, College Station, TX, USA) will be used for all analyses. Missing data and data from those who withdraw from the study will not be interpreted.

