### Procedures

#### Recruitment

Approximately 500 women present to CHBH each month for their first pregnancy US, of which 50% are < 25 weeks gestation. This offers a potential pool of 250 women per month to be included in the study. Participants will be recruited from women attending the Foetal Medicine Unit (FMU) at CHBH, where routine fetal ultrasound examinations are conducted. Eligible women will be resident within Soweto, aged 18 years and older, with a singleton pregnancy and presenting < 25 weeks gestation. Major fetal abnormalities detected during the first routine ultrasound examination conducted by an experienced radiologist in the FMU, or severe maternal morbidities, will exclude a pregnant woman from the trial. These women will be transferred to specialised clinical services at CHBH, where she will receive appropriate treatment.

Sample size calculations were based on detecting a 0.5-standard deviation (SD) difference between arms on both the Bayley III Language and Cognitive Scales, and *z*-scores for weight-for-age (WAZ), length-for-age (LAZ) and weight-for-length (WLZ) measured at 6 months of age at 90% power, which is 85 per arm. Allowing for 15% potential attrition during pregnancy and during follow-up to 6 months of infant age, the sample size in each of the three arms will be 100. This makes a total sample size of 300 women for recruitment.

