Child development at 6 months	Bayley Scales of Infant and Toddler Development, Third edition (Bayley III)	The total score from each developmental domain	Bayley III are an individually administered assessment of a child’s attainment of developmental milestones across five domains (i.e. cognitive, language, motor, social–emotional and adaptive skills) [47]. They have been recognised internationally as the most comprehensive tool to assess children from as young as 1 month old and have been validated in South Africa [48]	Individual scores to be compared between intervention and control groups using linear or logistic regression models dependent on the distribution of the data	End point
	Home Screening Questionnaire (HSQ)	HSQ score	The HSQ is a 30-item parent-report tool used to identify features of the home environments related to childhood development [49]. The HSQ has been validated and used for research purposes in a number of countries, including South Africa [50]	Individual scores to be compared between intervention and control groups using linear or logistic regression models dependent on the distribution of the data	End point
Secondary outcomes					
Mother/father–infant interaction at 6 months	Mother/father interaction rating scale	Interaction score	Rated from a 5-min videotape of mother/father and infant “talking and playing with each other”, with the infant in a high chair, the mother sitting on a chair at the same height opposite the infant and an attractive stack toy for them to share. We will use an adapted coding scheme developed by Richter et al. to code engagement (eye contact, joint attention), emotional tone, emotional regulation (maternal/paternal comforting for distress), maternal/paternal responsiveness and maternal/paternal scaffolding [51]	Individual scores to be compared between intervention and control groups using linear or logistic regression models dependent on the distribution of the data	End point
Infant growth at 6 weeks and 6 months	Weight and length	Weight (g) Length (cm) Weight-for-age *z*-score (WAZ) Length-for-age *z*-score (LAZ) Weight-for-length *z*-score (WLZ)	Infant growth will be measured using standard procedures for infant weight and length, and converted to *z*-scores using the 2006 WHO Growth Standards (WAZ, LAZ and WLZ)	Differences in mean weight and length of infants will be compared between intervention and control groups	Intermediate and end point

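### The rule to categorise non-normal scores and use logistic regression is unnecessary at this sample size, replaces the mean difference the trial is sized for, and is not covered by the stated 90% power

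*Protocol article*

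**What the plan says.** In the Data analysis section, the paragraph on the primary outcome makes linear regression the default when the data are normal. It then adds: "If not normally distributed, outcome data will be categorised and logistic regression methods will be used to assess differences". The same paragraph says: "Tests will be two-sided with a significance level of 0.05".

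Table 2 repeats the switch in its aggregation column for three measures: the Bayley III domain scores, the Home Screening Questionnaire (HSQ) score and the parent–infant interaction score. Each is to be compared using "linear or logistic regression models dependent on the distribution of the data". Table 2 does not state this switch for the other outcomes. Growth is compared by means, the Edinburgh depression score by proportions, and the rest as categorical data.

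The sample size under Recruitment rests on a difference in means only: "Sample size calculations were based on detecting a 0.5-standard deviation (SD) difference between arms", on Bayley Language and Cognitive and on growth z-scores, "measured at 6 months of age at 90% power, which is 85 per arm". With 15% attrition, "the sample size in each of the three arms will be 100". No sample size is given for a categorised outcome.

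**The concern.** The rule lets the shape of the outcome distribution decide whether a continuous score is kept or cut into categories. Linear regression does not need that protection. With about 85 infants per arm the difference in means is close to normally distributed even when individual scores are clearly skewed.

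Three things are at stake if the fallback fires on a Bayley score.

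- **The effect measure changes.** The trial was sized to detect a difference in means. The fallback reports an odds ratio, whose value depends on where the score is cut.
- **Domains may not be comparable.** The choice is made score by score, so one Bayley domain could be reported as a mean difference and another as an odds ratio.
- **The stated power no longer applies.** Grouping a score discards information, and the 85 per arm was not derived for a grouped outcome.

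**Working it through.** **Inputs.** From Recruitment: difference 0.5 SD, 90% power, 85 evaluable per arm, 15% attrition, 100 recruited per arm. From Data analysis: two-sided 5% level and no imputation, so about 85 per arm analysed. The cut points and distributions below are assumptions, because the article gives none.

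**1. The plan's own figure.** n = 2(z₀.₉₇₅ + z₀.₉₀)² / d² = 2(1.960 + 1.282)² / 0.25 = 84.1, rounded up to 85. Power at 85 is Φ(0.5·√(85/2) − 1.960) = Φ(1.30) = 90.3%, or 90.0% by the exact noncentral t. Attrition: 85/0.85 = 100. The stated 85 and 100 are correct, for a comparison of means.

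**2. Does skewness harm the comparison of means?** Simulated two-sample t-tests, 85 per arm, 20,000 runs, shift 0.5 SD:

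| Score distribution | Type I error | Power |
|---|---|---|
| Gamma, skewness 1.4 | 4.7% | 90% |
| Exponential, skewness 2 | 5.1% | 90% |

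Non-normality of this degree gives no reason to leave the linear model.

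**3. Power after a two-group split, near-normal score.** With cut c in control SD units, the proportions below the cut are p₁ = Φ(c) in control and p₂ = Φ(c − 0.5) in the intervention arm. With p̄ their average,

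power = Φ{ [ |p₁ − p₂|√85 − 1.960√(2p̄(1 − p̄)) ] / √(p₁(1 − p₁) + p₂(1 − p₂)) }.

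At the control median: [0.1915 × 9.220 − 1.960 × 0.694] / 0.681 = 0.595, and Φ(0.595) = 72%.

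| Cut | p₁ vs p₂ | Power | n per arm for 90% | Odds ratio |
|---|---|---|---|---|
| Control median | 50.0% vs 30.9% | 72% | 136 | 2.24 |
| Midway between arm means | 59.9% vs 40.1% | 73% | 133 | 2.23 |
| Control 25th percentile | 25.0% vs 12.0% | 59% | 186 | 2.44 |
| −1 SD | 15.9% vs 6.7% | 47% | 248 | 2.63 |

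Simulated logistic tests give 73% and 75% for the two central cuts and 45–49% at −1 SD. A split at the pooled sample median gives about 77–78%. The odds ratio moves with the cut although the underlying shift is always 0.5 SD.

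**4. Scores that would plausibly trigger the rule.** Simulated at 85 per arm with the same 0.5 SD shift:

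- Mild skew (±0.5): about 78% at a pooled-median split and 38–74% at low-score cuts, depending on the direction of skew.
- Strong skew, pooled-median split: 85% (gamma, skewness 1.4), 90% (lognormal, log-scale SD 0.5) and 92% (exponential).
- Strong right skew, cut at the control 25th percentile: 99–100%.
- Strong left skew, low cuts: 20–40%.

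**5. More than two categories.** Three or four ordered groups of a normal score, tested by a rank test as an approximation to ordinal logistic regression, keep about 83–84% power.

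**The case against.** The strongest reply is that the rule is conditional and the default is sound. Nothing in the article says the Bayley scores will be non-normal. If they are normal, the linear model is used and 90% power stands. This is right, and it limits the point to what happens if the fallback is used.

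A reader might go further and infer that the trial's power drops to about 75%, or below 50%. The documents do not support that as a general statement. Those figures come from a normal score, for which the rule would not fire. For strongly skewed scores a median split can lose little or nothing, and some cuts gain power. The wording also leaves room for an ordinal model, which loses less than a two-group split.

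A reader might also infer that cut points will be picked after the data are seen. The article does not say so. Cut points, number of categories and the normality criterion may stand in a full protocol or analysis plan that is not shown, so their absence is not a fault here. Only the choice of model is stated to depend on the data.

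Finally, it would be too broad to say that every outcome is affected. The sentence stands in the primary-outcome paragraph, and Table 2 gives the switch for Bayley, HSQ and interaction scores but compares growth by means.

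What remains is that the rule itself is stated, not left open. An analysis plan that followed it would inherit the change of effect measure, with no statistical need for it.

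**Conclusion.** The point holds as a criticism of a stated fallback for the primary Bayley scores and for the HSQ and interaction scores. The fallback is unnecessary: with skewness up to 2, comparing means at 85 per arm keeps about 5% type I error and about 90% power. If used, it replaces the 0.5 SD mean difference with an odds ratio and may split the Bayley domains across two scales.

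The stated 90% power does not carry over to it, but the loss has no single value:

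- near-normal or mildly skewed score, two groups: about 73–78% at a central split, about 38–74% at low cuts (16th–25th percentile or −1 SD);
- strongly skewed score, two groups: from about 20% to no loss or a gain;
- three or four ordered categories of a normal score: about 83–84%.

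These ranges assume a pure 0.5 SD shift, 85 analysed per arm, an unadjusted two-sided 5% test and illustrative cuts. The simulated values are good to a percentage point or two. The case for changing the rule does not depend on any one of them.

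**What to change.** Delete the categorisation sentence in Data analysis, and change the Table 2 aggregation cells for the Bayley, HSQ and interaction scores to match. State that these scores will be analysed by linear regression whatever their distribution, with robust (Huber–White) or bootstrap standard errors. Report the mean difference from control with its 95% confidence interval. This is the quantity the sample size was built on, so the 85 per arm needs no change on this account.

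Where a score is grossly skewed or piles up at a ceiling, add a rank-based or proportional-odds analysis as a sensitivity check, not as a replacement for the primary analysis. The growth row of Table 2 already compares means and needs no change here.

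The cost is wording and minor analysis work with standard options in the named software. No further data or participants are needed.

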### Design

Eligible mothers will be randomised to one of three arms: Arm 1, the control group, will receive standard practice of care during pregnancy; Arm 2 will receive the child development intervention at the first research ultrasound visit; and Arm 3 will receive the intervention at two research ultrasound visits. All mothers, infants and partners (where available) will be followed-up 6 weeks and 6 months postnatally for assessments. Participants will continue to receive routine antenatal, perinatal and postnatal care as provided by the tertiary care facility from which all participants are being recruited.

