### Intervention

Women will be randomised to one of three arms on recruitment at CHBH < 25 weeks gestation after having a fetal ultrasound examination as part of routine antenatal hospital services. The women will be blind to their arm allocation and remain blinded until study completion. Using computer-generated simple randomisation, each consecutive woman screened will be randomly allocated to a study arm. Research assistants responsible for screening will receive the study arm numbers for allocation from the study coordinator on a daily basis. The allocation sequence will be concealed from the research assistants enrolling the participants. Women recruited for Arm 1 will act as the control group and will receive one further standard US at DPHRU < 25 weeks gestation, when they will receive standard fetal growth measurements but no child development messages.

In addition to their routine antenatal US at CHBH, women recruited to Arm 2 will receive an additional US < 25 weeks gestation at DPHRU, during which they will receive messages to promote early childhood development. During the US session, the sonographer will talk with the mother and partner, if present, about the fetus’ sensory development and capacity for learning, fetal responsivity to the environment, maternal well-being and the dependence of the fetus on maternal and paternal health and well-being before and after birth.

In addition to their routine antenatal US at CHBH, women recruited to Arm 3 will receive two additional USs at DPHRU, one < 25 weeks gestation (early US) and another < 36 weeks gestation (late US). They will receive the same child development messages as mothers in Arm 2 at the first US. During the second US, in addition to childhood development messages, the sonographer will encourage the woman and her partner, if present, to personalise the baby, strengthen intentions to exclusively breastfeed, talk and sing to the child before and after birth, and counsel them on how to respond to their young infant’s emotional and learning needs.

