### Data collection

Study data will be collected and managed using REDCap (Research Electronic Data Capture) hosted by the University of the Witwatersrand. Data will be collected on the enrolled women, child and partners (where appropriate) at three stages: stage one, baseline at first research ultrasound visit at DPHRU < 25 weeks; stage two, 6-week postnatal follow-up; and stage three, 6-month postnatal follow-up. Data will be collected on tablets at stages one and two by two trained data collectors under the supervision of the study coordinator. At stage three, data will be collected by occupational therapists or physiotherapists trained in administering child development measures, under the supervision of the study coordinator. All data collectors will be trained on the principles of research ethics, Good Clinical Practice, referral procedures and management of difficult situations in the field.

Table 1 presents the schedule of enrolment, interventions and data collection.

**Table 1 Tab1:** Standard Protocol Items: Recommendations for Interventional Trials (SPIRIT) schedule of enrolment, interventions and data collection

	Study period				
	Enrolment	Intervention		Follow-up	
Timepoint	< 22 weeks GA	< 25 weeks GA	< 36 weeks GA	6 weeks postnatally	6 months postnatally
Enrolment					
Eligibility screen	X				
Informed consent	X				
Random allocation	X				
Interventions					
Early US		X			
Early US with messages		X			
Early and late US with messages		X	X		
Assessments: baseline and antenatal					
Socio-demographic questionnaire	X				
Fetal growth assessment		X	X		
Social support		X	X		
Maternal and paternal antenatal depression and anxiety		X	X		
Maternal and paternal antenatal attachment		X	X		
Maternal and paternal antenatal depression		X	X		
US experiences questionnaire		X	X		
Outcomes: primary and secondary					
Bayley Scales of Infant and Toddler Development, Third Edition					X
Home Screening Questionnaire					X
Mother/father–infant interaction					X
Perinatal and postnatal information				X	
Infant behaviour (crying, sleeping, etc.)				X	
Breastfeeding practices questionnaire				X	X
Maternal and paternal postnatal depression and anxiety				X	X
Social support				X	X
Partner involvement				X	X
Infant growth – weight and length				X	X
Immunisation status				X	X
Clinic attendance				X	X

*GA* gestational age, *US* ultrasound scan

The data collected at each stage is as follows:

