*Baseline at first research ultrasound scan at DPHRU.* Data at the first research visit (< 25 weeks) will include the participant’s contact details, demographic characteristics and reproductive history, socio-economic status, social and instrumental support, and breastfeeding intentions. Maternal and paternal fetal attachment is assessed using the Maternal and Paternal Attachment Scales [44, 45], and the mother and her partner, if available, will complete a social support questionnaire and the Edinburgh Postnatal Depression Scale [46]. The woman and her partner, if available, will also be asked to complete an ultrasound experience questionnaire after the US.
*Six-week postnatal follow-up.* Two trained outcome assessors, blind to the mother’s arm allocation, will complete the follow-up questionnaires with the mothers, infants and partners, where available. Questionnaires will assess perinatal and postnatal information, breastfeeding practices, and partner and social support. Postnatal depression will be assessed for the mother and partner using the Edinburgh Postnatal Depression Scale. Infant growth will be assessed using standard procedures for infant weight and length (the SECA 416 infantometer for length and the SECA 367 infant scale for weight). Measures will be converted to *z*-scores using the 2006 WHO Growth Standards for LAZ, WAZ and WLZ. Birth weight and length as well as key information on maternal and infant birth outcomes will be collected from the infant’s Road to Health Booklet.
*Six-month postnatal follow-up.* Occupational therapists or physiotherapists trained in child development will complete the 6-month follow-up assessments with the mothers, infants and partners, where available. The primary outcome for the 6-month follow-up is child development as measured by the Bayley Scales of Infant and Toddler Development, Third Edition [47].

All of the study outcome measures are presented in Table 2.

**Table 2 Tab2:** Study outcome measures

Outcome	Instrument	Measure	Description	Method of aggregation	Timepoint
Primary outcome					

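### Covariates enter the models only when arms are judged to differ at a baseline taken after randomisation; a short list fixed in advance should replace that trigger

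*Protocol article*

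**What the plan says.** In the protocol article, Data analysis, the outcome models are linear regression, or logistic regression after categorising if the outcome is not normally distributed. Two sentences govern covariates. The first sets the check: "Differences regarding baseline variables will be checked for clinical relevance between the three treatment groups". The second sets the consequence: "In case of relevant differences in baseline characteristics, additional adjustment(s) for these factors will be performed within the models to address potential confounding". No covariate is named, no threshold is given, and nothing is excluded from the pool of candidates.

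The timing of baseline is set elsewhere:

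- Intervention section, on allocation: "Women will be randomised to one of three arms on recruitment at CHBH < 25 weeks gestation".
- Same section, on method: "Using computer-generated simple randomisation, each consecutive woman screened will be randomly allocated to a study arm". No stratification is described.
- Data collection section, on baseline: "stage one, baseline at first research ultrasound visit at DPHRU < 25 weeks".
- Design section, on the same visit: "Arm 2 will receive the child development intervention at the first research ultrasound visit". Arm 3 also receives its first set of messages there.

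The data described for that visit include "demographic characteristics and reproductive history, socio-economic status", and also measures of the parents' state of mind: "Maternal and paternal fetal attachment is assessed using the Maternal and Paternal Attachment Scales", together with the Edinburgh Postnatal Depression Scale (EPDS) and a social support questionnaire. Only the ultrasound experience questionnaire is stated to follow the scan. Table 1 lists the socio-demographic questionnaire at enrolment, but attachment, depression and social support under the intervention visits.

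**The concern.** Under randomisation, a difference between arms in a characteristic fixed beforehand is chance. What makes such a covariate worth including is its relation to the outcome, not the size of its imbalance. A rule driven by imbalance leaves out strong predictors that happen to be balanced, may bring in weak ones that are not, and settles the model only after the arms have been compared. Since the text does not rank the adjusted and unadjusted results, two candidate answers to the primary question can exist.

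The timing of baseline adds a second problem. The Discussion section sets out a chain from ultrasound to attachment, to parent–infant interaction, to infant development. Attachment is thus a proposed mediator, and it is measured at the visit where the messages are given. If it were recorded after the messages, an arm difference in attachment could be an early effect of the intervention, yet under the rule it would count as an imbalance to be adjusted for. Table 2 also lists EPDS and partner involvement as outcomes with a baseline time point, so one visit supplies both outcomes and candidate adjusters.

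**Working it through.** **Inputs from the protocol article:** difference 0.5 SD, 90% power, 85 evaluable and 100 recruited per arm, 15% attrition (Recruitment section); two-sided 0.05 (Data analysis section). **Assumed, because the article gives no figure:** the share of outcome variance explained by covariates (R² = 0.1, 0.2, 0.3), the imbalance that would be called relevant (0.2 or 0.3 SD), and the mediator values in step 4.

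**1. The plan's own figure.** n = 2(1.960 + 1.282)²/0.5² = 84.1, so 85 per arm; 85/(1 − 0.15) = 100. Both reproduce. Power at 85 is Φ(0.5·√(85/2) − 1.960) = Φ(1.300) = 90.3%, or 90.0% by the t distribution.

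**2. How often the trigger would fire.** The SD of a chance difference in a standardised covariate is √(2/85) = 0.153. One covariate exceeds 0.2 SD with probability about 0.19, and 0.3 SD with probability about 0.05. With six independent covariates, at least one does so with probability 1 − 0.81⁶ ≈ 0.72 or 1 − 0.95⁶ ≈ 0.27. Whether any covariate enters thus depends heavily on a threshold that the plan does not state.

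**3. The stated rule against a fixed list.** Simulation of one two-arm comparison: 85 per arm, 4,000 runs per setting, six covariates of which three predict the outcome. The triggered model adds whichever covariates exceed the threshold. The fixed model always uses the three predictors.

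| R² | Trigger (SD) | Any selected | Power, unadjusted | Power, triggered | Power, fixed | Type I error, triggered | Type I error, better of unadjusted and triggered |
|---|---|---|---|---|---|---|---|
| 0.1 | 0.2 | 72% | 89% | 90% | 91% | 4.7% | 6.1% |
| 0.1 | 0.3 | 28% | 90% | 90% | 93% | 5.1% | 5.7% |
| 0.2 | 0.2 | 73% | 89% | 91% | 95% | 3.9% | 5.6% |
| 0.2 | 0.3 | 27% | 90% | 91% | 95% | 4.2% | 5.1% |
| 0.3 | 0.2 | 72% | 91% | 93% | 97% | 3.8% | 6.2% |
| 0.3 | 0.3 | 26% | 90% | 91% | 97% | 4.2% | 5.5% |

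The triggered estimate averaged 0.496 to 0.505 for a true 0.5, so it is unbiased. Simulation error is about √(0.9·0.1/4000) = 0.5 percentage points on power and √(0.05·0.95/4000) = 0.3 points on type I error. The fixed model here knows which covariates matter, so its gain is an upper guide. By formula, power with fixed covariates is Φ(3.260/√(1 − R²) − 1.960) = 93.0%, 95.4% and 97.4% for R² = 0.1, 0.2 and 0.3.

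**4. If a variable already changed by the messages were admitted.** Let the messages shift it by g SD, and let its slope on the outcome be b. The adjusted effect is 0.5 − g·b, with residual SD √(1 − b²).

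- g = 0.2, b = 0.2: effect 0.46 SD, power 86%.
- g = 0.3, b = 0.3: effect 0.41 SD, power 80%.
- g = 0.5, b = 0.4: effect 0.30 SD, power 57%.

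These values illustrate the mechanism. The article supplies neither g nor b.

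**The case against.** - **The adjustment is described as additional.** It follows the description of the regression comparison, so it can be read as a supplement to an unadjusted primary model. That reading is fair, but placing the adjustment within the models allows the other one too. The ambiguity stands and is part of the point.
- **A reader might infer that the rule will adjust the intervention effect away.** The documents do not support that. They do not say that attachment, EPDS or breastfeeding intentions were recorded after the messages. Naming one questionnaire as post-scan hints that the others came earlier, and women are described as blind to allocation, so answers given before the scan should not reflect the arm. Breastfeeding intention is the weakest example, because strengthening it is described for the late scan.
- **Not all baseline data can be affected.** Maternal age, parity and socio-economic status are natural baseline characteristics that one scan cannot change, and Table 1 places the socio-demographic questionnaire at enrolment. For these the second risk does not arise.
- **A reader might infer bias or a badly inflated error rate.** For true pre-treatment covariates the simulation shows neither. Even reporting the better of two p-values gave at most about 6.2%.
- **A reader might take the rise from 90% to 93%, 95% or 97% as what the rule costs.** That compares no adjustment with fixed adjustment. Against the triggered rule the gain is smaller.
- **The check is for clinical relevance, not significance.** This leaves room for prognostic judgement, but the judgement is still made after the arms are seen.
- **A covariate list is usual analysis-plan content.** Its absence is no finding. The trigger is different, because the protocol states it and fixes it badly.

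**Conclusion.** The point holds in a moderate form. The rule selects covariates on observed imbalance, leaves the model open until the arms have been compared, and does not say which result is primary. For pre-treatment covariates the cost is precision and analyst latitude: about 90–93% power under the triggered rule against 91–97% with fixed covariates. That rests on an assumed R² of 0.1 to 0.3, assumed triggers of 0.2 or 0.3 SD, and a two-arm simulation with independent covariates. The planned 90% power does not depend on adjustment, so the trial is not underpowered on this account.

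Admitting a variable that the arm has already changed is possible under the text, because baseline follows randomisation and nothing is excluded. It is a risk and not a certainty, since the order of the measures at that visit is not stated. Its size cannot be derived from the documents.

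**What to change.** Replace the trigger sentence with wording to this effect:

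- The primary model for each outcome, linear or logistic, adjusts for a short named list of prognostic covariates that the arm cannot affect and that are already collected. Examples are maternal age, parity, socio-economic status or education, and gestational age at the routine scan.
- The unadjusted result is reported alongside, and the adjusted one is named as primary.
- Attachment, EPDS and other measures from the research visit are not used as covariates unless recorded before the scan.
- Any adjustment prompted by observed imbalance is labelled as a sensitivity analysis.

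Infant age at assessment is best left off the list. It is measured after randomisation and would add little for growth z-scores that are already standardised for age.

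The cost is wording only. The list must be fixed before unblinding, which means committing to it without seeing the baseline table by arm. No new data are needed, and the 85 evaluable and 100 recruited per arm stand.
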